### **7.4. Management of AEs**

- (1) LOPM-related AEs

A small subset of patients may experience worsening lumbar symptoms or reduced mobility during LOPM, typically due to excessive force or abrupt manipulation irritating nerve roots. Recommended management will include:

- 1) Immediate rest in a supine position until symptom relief.
  - 2) Lumbar brace support during ambulation post-recovery.
  - 3) Analgesics (oral or intravenous) if symptoms persist, with resolution typically within 24 – 48 hours.
- (2) Drug-related AEs:

Gastrointestinal reactions (e.g., epigastric pain, nausea, constipation, vomiting), allergic reactions, or dependence/tolerance may occur. Management follows:

- 1) Reassessment of drug continuation based on causality.
  - 2) Discontinuation if warranted, with documented follow-up to monitor outcomes.
- (3) SAEs

For progressive symptoms (e.g., muscle weakness, cauda equina syndrome, or intractable pain):

- 1) Immediate clinical evaluation by a physician will be conducted.
- 2) Surgical intervention if clinically indicated will be conducted.
- (4) Protocol for AE Reporting

All AEs will require:

- 1) Prompt protective measures by investigators.
- 2) Notification of the IRB and lead research unit within 24 hours.
- 3) Signed, dated reports submitted per regulatory standards.

## **7.5. Analysis of AEs**

All cases of study withdrawal or treatment discontinuation due to AEs will be systematically documented. Data will include:

- (1) Demographics.
- (2) AE characteristics.
- (3) Timing relative to treatment.
- (4) Interventions attempted.
- (5) Final outcome.

## **7.6. Abnormal laboratory findings**

Investigators will evaluate the clinical significance of abnormal laboratory results and provide potential explanations. Abnormal laboratory findings attributable to previously reported AEs will be documented as part of the original AE record.

Independent AE reporting will be required for clinically significant abnormal laboratory results (excluding those linked to known AEs) meeting  $\geq 1$  of the following criteria:

- (1) Associated clinical symptoms (e.g., jaundice with elevated bilirubin).
- (2) Lead to adjustment of the investigational treatment (dose modification/discontinuation).
- (3) Require intervention (e.g., concomitant medication changes or additional therapies).

## **8. QC and quality assurance**

### **8.1. Analysis of study influencing factors**

The following factors will be rigorously controlled to ensure study validity and minimize bias:

- (1) Patient enrollment

Strict adherence to inclusion/exclusion criteria will be enforced through:

- 1) Protocol training for all investigators.
- 2) Centralized screening audits (10% random checks).

- (2) Standardization of LOPM

- 1) Operator qualification: All therapists will hold attending physician or higher credentials.
- 2) Competency assurance: Mandatory training and certification by the study team prior to participation

will be required.

(3) Lumbar rehabilitation guidance

Patients will receive:

1) Standardized exercise instruction (in-person demonstration).

2) Supplementary materials: Video tutorials and illustrated manuals (free access).

(4) Blinded outcome assessment

1) Role separation: Therapists and evaluators will be distinct personnel.

2) Blinding protocol: Evaluators will be masked to treatment allocation during assessments.

(5) Data entry quality

Dual-process verification:

1) Two dedicated staff per site will perform alternate data entry.

2) All entries will require double-confirmation before locking.

## **8.2. Infrastructure for QC**

To ensure data integrity and study compliance, this trial will establish a dedicated research laboratory, equipped with:

(1) Secure data management systems

1) Password-protected computers with encrypted storage for electronic CRFs and source documents.

2) Backup servers with daily automated updates to prevent data loss.

(2) Standardized hardware

1) Site-specific workstations configured with identical software to minimize operational variability.

2) High-resolution scanners for digitizing paper-based records (e.g., signed consent forms).

(3) Remote monitoring capacity

VPN-enabled devices for real-time access by auditors/regulators, ensuring compliance with GCP on-site inspection equivalency.

## **8.3. Study training and monitoring protocols**

To ensure rigorous adherence to study protocols and data accuracy, the following training and quality monitoring systems will be implemented:

(1) Three-tier QC system

1) First-level (site-level): Daily checks by research assistants for CRF completeness.

2) Second-level (center-level): Weekly audits by designated quality inspectors.

3) Third-level (study-wide): Monthly independent monitoring by external auditors.

(2) Research record verification

1) Dual independent data entry: Two research assistants will separately transcribe paper-based records into electronic CRFs, followed by consistency validation via electronic checks.

2) Real-time error correction: Discrepancies will be resolved through online source data verification with

timestamped corrections.

(3) Weekly patient management review

Key variables will be audited:

- 1) Subject ID accuracy.
- 2) Treatment completion status.
- 3) Investigator signatures.
- 4) Enrollment dates.

Data reporting plans will be updated weekly based on findings.

(4) Quality inspection procedures

Checklist-driven audits (weekly minimum) will cover:

- 1) Source documentation.
- 2) AE reporting compliance.
- 3) Investigational product accountability.

PI oversight: PI will review and sign all audit reports, with corrective actions documented.

(5) Monitoring plan

Bimonthly on-site monitoring: Two independent monitors will verify:

- 1) 100% source data against electronic CRFs for critical fields.
- 2) Protocol deviations and resolution logs.

Cross-center consistency checks will ensure uniform implementation.

#### **8.4. Strategies to improve participant compliance**

(1) Importance of compliance

Adherence monitoring: Participants will be required to attend all scheduled treatments, with protocol deviations (e.g., missed visits) documented, including:

- 1) Reasons for non-compliance (e.g., logistical barriers, side effects);
- 2) Corrective actions taken (e.g., rescheduling, re-education).

Patient education: Will emphasized the impact of consistent participation on treatment efficacy and safety outcomes.

(2) Common causes of non-adherence

Will be identified through pre-trial surveys and interim interviews:

- 1) Perceived lack of efficacy.
- 2) Misconceptions about recovery timelines.
- 3) Low trust in therapeutic protocols.

(3) Compliance optimization measures

1) Enhanced communication

Pre-treatment counseling: Will include detailed discussions about:

- ① Individualized treatment goals,
- ② Expected therapeutic trajectories.

2) Proactive follow-up

Structured phone calls at mid-treatment intervals will be used to:

- ① Address concerns (e.g., “Why hasn’t my pain improved?”).
- ② Reinforce protocol importance.

## **8.5. QC and quality assurance system**

(1) Primary-level (Site) quality checks

1) QC officer appointment: Each sub-center will appoint a qualified quality control officer responsible for weekly audits.

2) Checklist-based verification: The QC officer will evaluate:

- ① Source data documentation (e.g., CRFs, medical records).
- ② Investigational product accountability;
- ③ AE reporting compliance.

3) PI oversight: The PI will review and sign all QC reports weekly, with corrective actions documented for identified issues.

(2) Secondary-level (central) monitoring

1) Monitoring plan

① On-site visits: Will be conducted monthly by independent monitors, with frequency adjusted based on study progress/risk.

② 100% source data verification: Critical fields will be cross-checked against original records.

2) Monitoring procedures

Scope: will cover:

- ① Protocol adherence (e.g., informed consent, eligibility criteria);
- ② Drug dispensing logs;
- ③ AE/SAE handling timelines.

Monitor qualifications:

- ① Medical/clinical research background;
- ② Certified in GCP and electronic data capture (EDC) system operation.

On-site audits: Will Verify:

- ① Participant identity (e.g., ID checks).
- ② Data authenticity (e.g., lab reports, signed consents).

Electronic CRF Validation: Will ensure concordance between electronic CRFs and source documents.

Logic checks: Will include ad hoc reviews for implausible data (e.g., outliers in lab values).

Reporting: Post-visit reports will include:

- ① Findings;
- ② Actionable recommendations;
- ③ Resolution timelines.
- (3) Tertiary-level (Regulatory) audits

The study team will facilitate external audits by higher-tier institutions (e.g., ECs, funding agencies), providing:

- 1) Unrestricted access to source data.
- 2) Documentation of all QC/monitoring activities.

## **9. Data administration**

### **9.1. Source data documentation**

Source data will encompass all original records generated during the clinical study, including:

(1) Clinical source documents:

- 1) Medical charts.
- 2) Laboratory/test reports.
- 3) Pharmacy dispensing logs.
- 4) Signed informed consent forms.

(2) Derived study records:

- 1) Completed CRFs.
- 2) Data clarification forms.
- 3) Statistical analysis reports with raw datasets.

Requirements:

- (1) Retention: Will be stored for  $\geq 5$  years post-trial completion.
- (2) Accessibility: Must be available for regulatory inspection/auditing.
- (3) Verification: 100% source data verification will be performed for critical efficacy/safety endpoints.

### **9.2. Data recording and reporting standards**

Timeliness:

- (1) All source data must be transcribed into CRFs within 24 hours of collection.
- (2) Electronic CRF submission via web-based EDC systems within 72 hours, with automated timestamping.

Quality standards:

- (1) Entries must be contemporaneous, legible, and complete (no undocumented corrections).

(2) Dual verification: Critical fields (e.g., primary endpoints, SAEs) will require independent review by a second investigator.

System oversight:

Data managers (QC team) will perform:

- (1) Real-time validation (range/consistency checks).
- (2) Query resolution for discrepancies (e.g., missing/outlier data).
- (3) Database locking after final audit.

### **9.3. Source document archiving standards**

(1) Storage protocols

1) Active studies: Source documents will be maintained in secure, access-controlled research offices at each clinical site.

2) Completed studies: Documents will be transferred within 30 days to a centralized archive with:

- ① Climate-controlled environments (temperature/humidity monitoring),
- ② Fireproof/waterproof storage systems.

(2) Access security

1) Role-based permissions:

- ① Investigators: Will have read/write access during active trials.
- ② Monitors/auditors: Will have read-only access for verification.
- ③ Third parties: Will require IRB approval for access.

2) Electronic records: Will be protected via two-factor authentication and encrypted backups.

(3) Retention period

1) Minimum duration: 5 years after study completion, or longer if required by:

- ① Local regulations (e.g., China's Regulations on Human Biomedical Research).
- ② Sponsor/funding agency policies.

2) Destruction protocol: Documents will be shredded/electronically erased with witnessed documentation.

### **9.4. Source document access regulations**

(1) General access policy

Access to source documents must comply with:

- 1) Institutional policies of the hosting hospital.
- 2) Archival regulations of the clinical trial unit.

(2) On-site monitoring procedures

1) Facilitated access: Clinical sites must provide immediate, unhindered access to source documents for monitors during scheduled visits.

2) Designated review area: Inspection will occur in a secured, monitored space to ensure:

- ① Document integrity (no unauthorized removal);
- ② Patient confidentiality (no public exposure).

(3) Copying of source documents

1) Redaction requirement: All copies must have personally identifiable information removed, including:

- ① Names;
- ② ID numbers;
- ③ Contact details.

2) Authorization: Copies will require written approval from the PI and IRB.

### **9.5. Data verification protocol**

(1) Electronic data review process

Monitors must:

1) Access the monitor interface of the EDC system.

2) Verify 100% of critical fields (e.g., primary endpoints, SAEs) against source documents (e.g., medical records, lab reports).

3) Mark each data field as "reviewed" in the EDC system, with automated timestamps.

(2) Discrepancy management

1) Query initiation: If inconsistencies are identified, monitors must:

- ① Generate electronic queries (e.g., via EDC or dedicated data clarification forms).
- ② Specify the exact variance.

2) Resolution tracking:

- ① Site investigators will respond within 72 hours with corrections/justifications.
- ② All queries will be closed-loop documented in the EDC audit trail.

### **9.6. CRF completion guidelines**

(1) Completion protocol

1) Exclusive responsibility: CRFs must be filled directly by investigators (not delegated to non-clinical staff).

2) Real-time documentation: Data must be recorded during or immediately after patient visits to ensure:

- ① Timeliness ( $\leq 24$  hours post-encounter);
- ② Accuracy (no retrospective entries);
- ③ Completeness (all protocol-required fields).

(2) Correction standards

1) Error modification: Any changes will require:

- ① Single strikethrough of original entry (no obscuring);
  - ② Legible annotation of corrected value;
  - ③ Investigator's signature + date;
  - ④ Brief rationale.
- 2) Prohibition: No erasures, white-out, or overwriting will be permitted.

(3) Quality assurance

1) Dual review:

- ① Site PIs will verify 100% of CRFs for:

Protocol compliance and consistency with source documents.

- ② Central monitor will audit 10% randomly (higher risk for critical fields).

2) Electronic backups: Scanned CRFs will be archived in read-only PDF/A format.

## **9.7. Electronic data reporting protocol**

(1) Roles and Responsibilities

Electronic CRF entry personnel:

1) Each study site must appoint two trained electronic CRF entry specialists responsible for:

- ① Reviewing source documents (e.g., research charts) for completeness and accuracy.
- ② Entering data into the electronic CRF system.

2) Qualifications:

- ① Certified in good clinical practice (GCP);
- ② Completed protocol-specific electronic CRF training.

(2) Data flow process

1) Investigator documentation:

After each patient visit, the investigator must complete the research chart by end-of-day and hand it to the electronic CRF entry team.

2) Electronic CRF entry and validation:

- ① Primary entry: The first electronic CRF specialist will enter data into the system within 24 hours.
- ② Secondary verification: The second specialist will independently:

Cross-checks 100% of entries against source documents and resolve system-generated queries (e.g., missing data, outliers).

(3) Correction and audit trail

1) Error handling:

- ① Any corrections must be annotated with a reason (e.g., "Transcription error");
- ② Signed/dated by both the investigator and electronic CRF specialist.

2) Audit trail:

The electronic CRF system will log all modifications with:

- ① Timestamp;
- ② User ID;
- ③ Justification for changes.

## **9.8. Database review and locking procedures**

(1) Data cleaning & query resolution

Data manager responsibilities:

- 1) Review all resolved queries from data clarification forms and update the database accordingly.
- 2) Issue new data resolution queries if inconsistencies persist.
- 3) Document all changes in the audit trail, including:

- ① Investigator's response;
- ② Date of resolution;
- ③ Data manager's verification signature.

(2) Database locking process

1) Pre-lock checks:

- ① 100% verification of critical variables (primary/secondary endpoints, SAEs).
- ② Blinded review: An independent statistician will confirm data integrity without access to treatment allocation.

2) Final lock approval:

- ① PIs and statistician will sign off on the data quality assurance report.
- ② Database will be permanently locked with write-access disabled.

3) Statistical handoff:

- ① Read-only copy will be transferred to the biostatistics team.
- ② Metadata + audit logs will be archived separately for regulatory inspection.

## **10. Statistical analysis**

An independent third party (Institute of Basic Research in Clinical Medicine, China Academy of Chinese Medical Sciences) will perform all statistical analyses. The primary analysis will follow the ITT principle, including all randomly assigned patients. A supporting per-protocol (PP) analysis will be conducted to assess the robustness of the primary findings.

### **10.1 Basis for protocol development**

This study protocol of statistical analysis has will be developed in accordance with the following guidelines and requirements:

(1) China's Guidelines for Biostatistics in Clinical Trials.

(2) China's GCP guidelines.

(3) The Technical Guidelines for Pharmaceutical Research in Various Stages of New Traditional Chinese Drug Development (Trial) issued in 2020.

(4) The specific project requirements of the National Key Research and Development Program of China.

## **10.2 Analysis populations**

### **10.3 Safety analysis population**

The safety analysis set will include all randomized subjects who received at least one time of the assigned study intervention. All safety evaluations-including the recording, documentation, and analysis of any AEs or reactions-will be performed on this population.

### **10.4 ITT**

The ITT population will include all randomized participants. The primary analyses will be based on the ITT principle to preserve the unbiased nature of the randomization and to provide a conservative estimate of the treatment effect under real-world clinical conditions.

### **10.5 PP**

The PP population will be required to satisfy all the following criteria:

(1) Are correctly randomized and receive at least one time of the study intervention.

(2) Have no major protocol deviations (pre-specified) that could substantially impact the efficacy evaluation (e.g., major violations of inclusion/exclusion criteria discovered post-randomization, use of prohibited concomitant therapies, or compliance below a pre-defined threshold).

(3) Complete the assessment for the primary efficacy endpoint.

### **10.6 Statistical method**

The primary efficacy analysis will follow the intention-to-treat (ITT) principle, including all randomly assigned patients. All analyses will be performed using R software, version 4.4.0 (R Foundation for Statistical Computing). Missing data for the longitudinal outcomes will be handled under the assumption of missing at random using multiple imputation. Imputation will be performed using the Multivariate Imputation by Chained Equations (MICE) package in R, generating 5 imputed datasets. The imputation model will include all longitudinal outcome measures from all-time points and all baseline covariates listed above. Results from the imputed datasets will be pooled according to Rubin's rules. Baseline characteristics will be summarized using descriptive statistics. For the continuous outcomes, between-group differences at each specific time point and within-group changes from baseline will be evaluated via pairwise comparisons of the estimated marginal means derived from the linear mixed model (LMM), which will be fitted using the lme4 package (version 1.1.35). These comparisons will be conducted using the emmeans package (version 1.10.0) with Tukey's method for adjustment of P values to control the

family-wise error rate. The model will include fixed effects for treatment group, time (modeled as a categorical factor), and their interaction. The model will be adjusted for the following prespecified baseline covariates: sex, age, body mass index, total duration of lumbar disc disease, duration of the current progressive episode, and degree of herniation at the symptomatic disc level. For categorical outcomes, between-group comparisons will be performed using the chi-square test or Fisher's exact test as appropriate, while the Bonferroni correction will be applied to adjust the significance level and control for type I error arising from multiple comparisons. All statistical tests will be two-sided, with a P value of less than .05 considered statistically significant. Institute of Basic Research in Clinical Medicine, China Academy of Chinese Medical Sciences will perform all statistical analyses.

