### **3.2. Sample size**

The sample size was calculated using PASS (Power Analysis and Sample Size), version 11 (Number Cruncher Statistical Systems). The calculation was based on detecting a MCID of 7 points on Oswestry Disability Index (ODI), with a standard deviation of 15.1 points derived from a pre-trial study. A statistical power of 90% and a two-sided alpha of 0.05 were assumed. The calculation was based on the primary objective of demonstrating the superiority of the combination therapy over YBT or LOPM alone, using the Dunnett's test for the two primary comparisons. The initial calculation indicated a requirement of 113 participants per group. After accounting for a 15% dropout rate, the sample size was set at 133 participants per group. To ensure robust multi-center recruitment, the target sample size was further increased to 146 participants per group.

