## **6. Observation endpoints and clinical outcomes**

### **6.1. Clinical observation endpoints**

Efficacy measures will be recorded at baseline and 3 days, 1 week, 2 weeks, 6 weeks, 14 weeks, and 26 weeks after randomization. The measurement instruments will be ODI for the functional disability, VAS for the leg and low back pain, and 12-Item Short Form Health Survey (SF-12) for the quality of life. Blood routine tests and liver and kidney function tests will be conducted before randomization and at 2 weeks after randomization. In addition, detailed records of each patient's gastrointestinal discomfort, skin

allergies, and other adverse events will be collected at 2 weeks after randomization to assess safety. At the 26-week post-randomization follow-up, a repeat MRI will be performed. The change in the sagittal area of the disc herniation from baseline to 26 weeks will be measured, with a reduction of  $\geq 40\%$  defined as the occurrence of disc resorption. The disc resorption rates will be calculated. The primary outcome will be change in ODI from baseline to week 2. The minimal clinically important difference (MCID) for ODI will be set at  $\geq 7$  points, consistent with prior studies. Secondary outcomes will include leg and low back pain VAS, SF-12, adverse events, and disc resorption rates.

(1) ODI

ODI assesses the effect of pain on normal daily activity including the ability to and intensity of lifting, care for oneself, walk, sit, sexual function, stand, social life, sleep and travel, ranging from 0 (no disability) to 100 (maximum disability possible).

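### Fixing 5 imputations leaves avoidable Monte Carlo noise in the week-2 ODI contrasts; error control is intact, but a borderline verdict can change with the seed

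*Protocol*

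**What the plan says.** Protocol section 10.6 sets the missing-data method for the longitudinal outcomes: "Missing data for the longitudinal outcomes will be handled under the assumption of missing at random using multiple imputation". It fixes the number of draws: "Imputation will be performed using the Multivariate Imputation by Chained Equations (MICE) package in R, generating 5 imputed datasets". Pooling is also fixed: "Results from the imputed datasets will be pooled according to Rubin's rules".

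This reaches the primary result. Section 6.1 states "The primary outcome will be change in ODI from baseline to week 2", and section 10.6 states "The primary efficacy analysis will follow the intention-to-treat (ITT) principle, including all randomly assigned patients", so a missing week-2 ODI is imputed. The group contrasts come from the linear mixed model with Tukey-adjusted P values, judged against a fixed line: "All statistical tests will be two-sided, with a P value of less than .05 considered statistically significant".

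The only figure for data loss is in section 3.2: "After accounting for a 15% dropout rate, the sample size was set at 133 participants per group". It is not tied to a visit. The protocol gives no reason for choosing five imputations.

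**The concern.** With m imputations, the pooled estimate is an average of m random draws. With the data held fixed, a different random seed gives a different estimate, a different between-imputation variance (on m − 1 = 4 degrees of freedom here) and so a different adjusted P value. If that P value lies near .05, the declared result for combination therapy against YBT or LOPM alone may turn on the seed. This noise comes from computation, not from patients, and more imputations remove most of it.

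**Working it through.** **Inputs from the protocol.** Section 3.2: difference 7 ODI points, SD 15.1, power 90%, two-sided alpha 0.05, Dunnett's test for two comparisons, 113 per group, 15% dropout, 146 per group. Section 10.6: m = 5, Rubin's rules, Tukey adjustment over three arms, P < .05.

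**The plan's own figure.** The two-sided Dunnett critical value for two comparisons is 2.212 and z at 90% power is 1.282. Then n = 2 × (15.1 × (2.212 + 1.282) / 7)² = 113.6. The stated 113 has 89.8% power, so it is reproduced to rounding. 113 / 0.85 = 132.9, giving 133, and 3 × 146 = 438. The choice of five imputations has no derivation to reproduce.

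**Assumptions.** The protocol gives no FMI for week 2. I use 0.03 to 0.15. The upper end corresponds to 15% of week-2 values missing (0.15 × 146 = about 22 per arm). Complete-data degrees of freedom are taken as 429.

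**Step 1: seed noise in the estimate.** For fixed data, SD over seeds / SE = √(FMI / m).

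| FMI | m = 5 | m = 50 |
|---|---|---|
| 0.03 | 0.077 | 0.024 |
| 0.05 | 0.100 | 0.032 |
| 0.10 | 0.141 | 0.045 |
| 0.15 | 0.173 | 0.055 |

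**Step 2: effect on a borderline verdict.** Write W for the within-imputation variance, and let the between-imputation variance B vary over seeds as FMI × χ²(m − 1)/(m − 1), with total variance scaled to 1. The total is T = W + (1 + 1/m)B, referred to Barnard–Rubin degrees of freedom and the three-arm Tukey threshold. Share of seeds giving P of .05 or more:

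| FMI | long-run P = .03, m = 5 | long-run P = .04, m = 5 | P = .04, m = 20 | P = .04, m = 50 |
|---|---|---|---|---|
| 0.03 | 1% | 17% | 2% | 0% |
| 0.05 | 6% | 26% | 6% | 1% |
| 0.10 | 18% | 37% | 17% | 5% |
| 0.15 | 27% | 43% | 24% | 11% |

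At a long-run P of .02 with m = 5, the share is 0% at FMI 0.03 and 13% at FMI 0.15.

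**Step 3: direct check.** Single data sets (146 per arm, assumed within-patient correlation 0.5 or 0.7, Bayesian regression imputation, ANCOVA at week 2) were re-imputed under 400 seeds at m = 5 and 100 seeds at m = 50, with the long-run P set at .04.

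- 15% missing (FMI 0.14 to 0.16), m = 5: the central 95% of P values ran from about .012–.014 to .13–.15, and 56% to 60% of seeds were significant.
- 15% missing, m = 50: about .029 to .055, and 88% to 89% significant.
- 5% missing (FMI about 0.05), m = 5: about .023 to .077, and 70% to 74% significant.

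This agrees with step 2.

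**Step 4: how often it matters over all trials.** SE of a contrast = 15.1 × √(2/146) / √(1 − FMI), which is 1.79 points at FMI 0.03 and 1.92 at FMI 0.15. The probability, per contrast, that the decision differs from the one at very large m, from FMI 0.03 to 0.15:

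| True effect | m = 5 | m = 50 |
|---|---|---|
| 7 points | 0.8% to 3.8% | 0.2% to 0.9% |
| 4.5 points (power about 50% to 56%) | 2.6% to 7.7% | 0.8% to 2.1% |
| none | 0.3% to 0.9% | 0.1% to 0.3% |

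Power at 7 points falls by 0.2 points at FMI 0.03 (93.9% to 93.8%, rounded) and by 1.9 points at FMI 0.15 (90.3% to 88.4%) when m goes from very large to 5. With no effect, the rejection rate per contrast is about 1.9% at m = 5, at m = 50 and at very large m.

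**The case against.** The strongest reply is that the planned analysis is valid as written. Rubin's rules add the (1 + 1/m)B term and use a t reference, so finite m is already paid for in the standard error and degrees of freedom. That stands: step 4 shows no change in type I error and little loss of power.

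A reader might go further than the documents allow in four ways.

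- **That the conclusion rests on the seed instead of the data.** It does not. The seed matters only when the data have already put the result near .05, and the 17% to 43% is conditional on that. The figures over all trials are those in step 4.
- **That 15% of week-2 ODI will be missing.** Section 3.2 attaches no visit to its dropout figure, follow-up runs to week 26, and week 2 is the end of treatment. Section 10.6 also puts outcomes from all time points into the imputation model, which lowers the FMI. So 0.15 is an upper assumption. At 0.03 the borderline figure is still 17%.
- **That later visits fare worse by a known amount.** More missing data by week 26 is plausible, but the protocol gives no rate for any visit, so no size can be attached.
- **That the absence of a stated seed is a defect.** A seed is commonly set in the SAP, which is not at hand. Fixing one makes a run repeatable but does not reduce the noise from five draws.

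It is also fair to say that 50 is not a unique answer. At FMI 0.15 and long-run P of .04, it still leaves 11% of seeds on the other side of the line, and 100 leaves 4%. At a long-run P of exactly .05, no number of imputations settles the verdict.

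**Conclusion.** The point holds as a low-severity matter of reproducibility. The protocol itself fixes five imputations for the primary analysis, and this leaves seed noise of about 0.08 to 0.17 standard errors in the week-2 contrasts. The consequence is confined to borderline results and to a small loss of power; no bias and no loss of error control is shown.

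The sizes rest on an assumed FMI of 0.03 to 0.15, the protocol's SD of 15.1 and 146 per arm, and the Tukey threshold in section 10.6. If almost no week-2 ODI is missing, the effect nearly disappears.

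**What to change.** In section 10.6, change the number of imputed data sets from 5 to at least 50. With the same FMI range, this cuts seed noise to 0.02 to 0.055 standard errors and recovers nearly all of the lost power. It needs one phrase and some minutes of computing, with no patients, no extra data and no change of design. The random seed, and a report of Monte Carlo error for the primary contrasts if wanted, can be set in the SAP.

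### The listed imputation predictors omit randomised treatment group, which biases the week-2 ODI difference towards zero by at most about the fraction missing at week 2

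*Protocol*

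**What the plan says.** The primary endpoint is set in Protocol section 6.1: "The primary outcome will be change in ODI from baseline to week 2". Section 3.2 powers the trial for a 7-point ODI difference with a standard deviation of 15.1, and allows for 15% dropout without saying when it occurs.

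Section 10.6 fixes the handling of missing data in some detail:

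- Assumption and approach: "Missing data for the longitudinal outcomes will be handled under the assumption of missing at random using multiple imputation".
- Software and number of data sets: "Imputation will be performed using the Multivariate Imputation by Chained Equations (MICE) package in R, generating 5 imputed datasets".
- Predictors: "The imputation model will include all longitudinal outcome measures from all-time points and all baseline covariates listed above".

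The only covariate list in that section comes after this sentence, not before it: "sex, age, body mass index, total duration of lumbar disc disease, duration of the current progressive episode, and degree of herniation" at the symptomatic level. The word 'above' is a drafting slip and does not bring group in.

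The analysis model applied to the completed data is described in the same section: "The model will include fixed effects for treatment group, time (modeled as a categorical factor), and their interaction".

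**The concern.** An imputation model should contain at least the terms that the analysis model is meant to estimate. Here the analysis estimates group and group-by-time effects, while the stated imputation model knows a patient's group only through whatever other scores that patient has. For a patient who leaves before week 2, those scores carry little or none of the week-2 treatment effect. The imputed value is then much the same in every arm, and averaging it with the observed values shrinks the difference.

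The imputation step introduces this error itself. A likelihood-based mixed model with group, time and their interaction, fitted to the observed data, would not have it under the missing-at-random assumption that the protocol already makes. The result at stake is the primary one: the week-2 ODI comparison of the combination with each single therapy.

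**Working it through.** **Inputs from the protocol.** Difference 7, SD 15.1, two-sided alpha 0.05, power 90%, Dunnett's test for two comparisons, 15% dropout, 113 then 133 then 146 per group (section 3.2); 1:1:1 allocation (section 5.1); 5 imputed data sets (section 10.6).

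**Step 1: the plan's own figure.** Per-comparison power is Φ(δ / SE − c), with SE = 15.1 × √(2/n) and two-sided Dunnett c = 2.212. At n = 113, SE = 2.009, 7 / 2.009 = 3.484, and Φ(3.484 − 2.212) = Φ(1.272) = 0.898. At n = 114 it is 0.901. So 113 reproduces within rounding. Then 113 / 0.85 = 132.9, giving 133, and 3 × 146 = 438.

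**Step 2: first-order size of the bias.** Let f be the fraction missing at week 2. If those patients have no post-baseline data, their imputed values show no group difference, so the expected estimate is (1 − f) × 7 + f × 0:

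| f | Expected estimate |
|---|---|
| 3% | 6.79 |
| 5% | 6.65 |
| 10% | 6.30 |
| 15% | 5.95 |

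**Step 3: simulation check.** Three arms of 146, chained-equation imputation with 5 data sets, 150 replicates per scenario, baseline-adjusted week-2 difference, Monte Carlo SE about 0.1. Assumptions not in the protocol: exchangeable correlation r between visits; effects of 2, 4 and 7 points at day 3, week 1 and week 2, and 7 thereafter; equal missingness across arms. With 15% missing at week 2:

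| Pattern | Group omitted (r = 0.3 / 0.5 / 0.7) | Group included (r = 0.3 / 0.5 / 0.7) |
|---|---|---|
| All post-baseline ODI missing | 5.90 / 6.14 / 5.91 | 7.11 / 7.12 / 7.10 |
| Dropout after week 1 | 6.14 / 5.94 / 6.19 | 7.13 / 6.82 / 7.03 |
| Only week 2 missing | 6.28 / 6.49 / 6.84 | 6.93 / 6.99 / 6.97 |

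With all post-baseline ODI missing and r = 0.5, omitting group gave 6.58 at 5% missing and 6.39 at 10%, consistent with step 2. A separate simulation let dropout build up to 15% by week 26, with 3–5% missing at week 2. It gave 6.7 to 6.8 without group and 6.8 to 7.1 with it.

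**Step 4: could VAS and SF-12 stand in for group?** Three further outcomes were added, correlated 0.5 with ODI and with the same standardised effect, at 15% missing. For dropouts they did not help: 6.0 without group against 7.2 with it when all post-baseline data were missing, and 6.2 against 7.1 after week 1. A patient who leaves loses all scales together. They helped only when week 2 alone was missed (6.8 against 7.1).

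**Step 5: power at 146 per group.** SE = 15.1 × √(2/146) = 1.767, held fixed as an approximation. Section 10.6 plans Tukey's adjustment (critical value about 2.35), so both versions are shown.

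| Mean estimate | Estimate / SE | Dunnett power (c = 2.212) | Tukey power (c = 2.35) |
|---|---|---|---|
| 7.00 | 3.961 | 0.960 | 0.946 |
| 6.79 (3% missing) | 3.842 | 0.948 | 0.932 |
| 6.65 (5% missing) | 3.763 | 0.939 | 0.921 |
| 5.95 (15% missing) | 3.367 | 0.876 | 0.845 |

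On the more cautious basis of 124 per group (146 × 0.85), SE = 1.918, and Dunnett power goes from 0.925 at 7 points to 0.813 at 5.95.

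**The case against.** **The list may not be exhaustive.** The sentence says what the imputation model includes and does not say that nothing else enters. A statistical analysis plan, not shown here, may add group. That is possible, and it is why the point concerns the text as written. It does not remove the point: the protocol chose to list the predictors and left out the one that the analysis most needs.

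**The 15% is not a week-2 figure.** This stands. Section 3.2 attaches no time to the dropout rate, follow-up runs to 26 weeks, and the primary endpoint falls at the last visit of the treatment period. A reader might infer that the primary effect will be understated by about 15% and power will fall well below 0.90. The protocol does not support that as the expected case.

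**The bias is conservative, and the sample has been enlarged.** This also stands. Shrinkage towards zero does not create a false positive in a superiority trial, and the increase from 133 to 146 per group absorbs much of the plausible loss of power. It is still an avoidable error in the primary estimate.

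**The number of imputations.** A reader might also infer from "generating 5 imputed datasets" that the primary verdict could change with the random seed. That has not been shown. In one simulated data set chosen as borderline, repeated runs with 5 imputations gave P from 0.008 to 0.041 (5th to 95th percentile), all below .05, and this result was not independently reproduced. With 15% missing information, the relative efficiency of 5 imputations is 1 / (1 + 0.15/5) = 0.97.

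**Conclusion.** The point holds as a should-fix. The stated imputation predictors omit randomised group while the analysis estimates group and group-by-time effects, so the week-2 ODI difference is pulled towards zero by at most about the fraction missing at week 2. For a true 7 points, the estimate is about 6.6 to 6.8 with 3–5% missing, and Dunnett per-comparison power falls only from 0.96 to about 0.94–0.95. In the worst case, with the whole 15% missing at or before week 2, it is about 5.9 to 6.8. The lower end applies to patients with no week-2 or later scores, the upper end to those who miss week 2 only. At 5.95 points, power is about 0.88.

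The size rests on equal missingness across arms, the assumed correlations and effect profile, and a week-2 missing fraction that the protocol does not give. The shrinkage appeared in every scenario with group omitted, although when only week 2 was missing and r = 0.7 it was within simulation error. Including group brought the estimate back to about 7.

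**What to change.** Replace the predictor sentence in section 10.6 with: *The imputation model will include randomised treatment group, every longitudinal outcome at every time point, and all baseline covariates listed below.* With the data in wide format (one column per visit), group as a predictor of each visit's score carries the group-by-time effect, so no further interaction term is needed for that purpose.

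Imputing separately within each arm with centre added is not advised here. Counting SF-12 as two scores, five outcomes at seven time points leave 34 other scores as predictors of each imputed one. Six covariates and 12 centre indicators bring this to at least 52, on at most 146 patients per arm.

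Using more than 5 imputations is an optional, inexpensive way to reduce seed-to-seed variation. The main change costs one sentence in the protocol, and in the analysis plan if it repeats the list. It needs no new data and should be made before the database is locked.
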